## Abstract

**Introduction:**

Calcium channel blockers (CCB), a commonly prescribed antihypertensive (AHT) medicine, may be associated with increased risk of breast cancer. The proposed study aims to examine whether long-term CCB use is associated with the development of breast cancer and to characterise the dose–response nature of any identified association, to inform future hypertension management.

**Methods and analysis:**

The study will use data from 2 of Australia’s largest cohort studies; the Australian Longitudinal Study on Women’s Health, and the 45 and Up Study, combined with the Rotterdam Study. Eligible women will be those with diagnosed hypertension, no history of breast cancer and no prior CCB use at start of follow-up (2004–2009). Cumulative dose-duration exposure to CCB and other AHT medicines will be captured at the earliest date of: the outcome (a diagnosis of invasive breast cancer); a competing risk event (eg, bilateral mastectomy without a diagnosis of breast cancer, death prior to any diagnosis of breast cancer) or end of follow-up (censoring event). Fine and Gray competing risks regression will be used to assess the association between CCB use and development of breast cancer using a generalised propensity score to adjust for baseline covariates. Time-varying covariates related to interaction with health services will also be included in the model. Data will be harmonised across cohorts to achieve identical protocols and a two-step random effects individual patient-level meta-analysis will be used.

**Ethics and dissemination:**

Ethical approval was obtained from the following Human research Ethics Committees: Curtin University (ref No. HRE2022-0335), NSW Population and Health Services Research Ethics Committee (2022/ETH01392/2022.31), ACT Research Ethics and Governance Office approval under National Mutual Acceptance for multijurisdictional data linkage research (2022.STE.00208). Results of the proposed study will be published in high-impact journals and presented at key scientific meetings.

**Trial registration number:**

NCT05972785.

STRENGTHS AND LIMITATIONS OF THIS STUDYThis study will characterise any dose–response nature of the association between calcium channel blockers (CCB) use and breast cancer.To minimise the impact of confounding by indication, the study will be limited to participants with diagnosed/self-reported hypertension and comparisons will include participants exposed to other prescribed (non-CCB) antihypertensive medicines in addition to those who have no pharmacotherapy for hypertension.Complete ascertainment of prior exposure will not be possible since we will not have lifetime capture of prescribing data; therefore, CCB exposure may be under-reported.The diagnostic interval of breast cancer may vary between Australian and Dutch women, particularly since case ascertainment through cancer registries can take months from the initial diagnosis to coding notifications.

## Introduction

Breast cancer has overtaken lung cancer as the most common cancer and the leading cause of death in women globally, accounting for 2 million new cases and 685 000 deaths worldwide in 2020.^1^ By 2040, breast cancer is expected to increase by 40% to more than 3 million new cases and 1 million deaths annually.^2^ Breast cancer places a significant burden of disease, excess mortality and reduced quality of life on women and the broader health system; identifying and mitigating potentially modifiable risk factors are a critical strategy in reducing this burden.

Hypertension is a well-established, modifiable risk factor for stroke and other cardiovascular events and a major contributor to chronic diseases such as heart failure, chronic kidney disease and retinopathy.^3^ Worldwide, hypertension causes more deaths and morbidity than any other biomedical risk factor.^4^ Cardiovascular disease is responsible for approximately 17 million deaths a year, nearly one-third of total mortality globally.^5^ Together with three other AHT medicines (ie, ACE inhibitors (ACEI), angiotensin receptor blockers (ARB) and thiazide or thiazide-like diuretics), dihydropyridine calcium channel blockers (CCBs) have been recommended for initiation as first-line therapy in many countries.^6 7^

It has been hypothesised that CCBs may increase the risk of cancer by changing intracellular calcium levels, thereby affecting the process of apoptosis (programmed cell death), disabling the destruction of mutated cells and leading to development of diseases such as cancer in which there is indiscriminate replication of a mutated cell.^8^ Calcium is known to play a regulatory role in apoptosis via multiple biochemical/pharmacological pathways.^9–11^ It has been postulated that, due to its secretory nature, breast tissue may be more vulnerable to alterations in apoptotic activity than other tissue, leading to complex hormone-related relationships between apoptosis and breast carcinoma.^12^ In addition, one particular CCB, nifedipine, has been found to increase proliferation and migration of breast cancer cells in vitro^13^ and to reduce resting calcium concentration and apoptotic gene expression in mice.^14^

In 2017, we published a systematic review and meta-analysis^15^ highlighting the uncertainty regarding the association between long-term use of CCBs and breast cancer, primarily due to the limited availability of long-term follow-up data. This review and meta-analysis found that the literature is equivocal on whether CCBs are a risk factor for breast cancer. Li *et al*
16 reported that long-term (>10 years) use of CCBs was associated with a 2.4-fold (95% CI 1.2 to 4.9) increased risk of invasive ductal breast cancer and 2.6-fold (95% CI 1.3 to 5.3) increased risk of invasive lobular breast cancer. In contrast, Grimaldi-Bensouda *et al,*
17 using data from the UK, and Wilson *et al*,^18^ using data from the USA, from sisters with and without breast cancer failed to find an association between CCB use and breast cancer (OR 0.95 (95% CI 0.87 to 1.04) and HR 0.88 (95% CI 0.58 to 1.33), respectively). A similar pattern was observed in a recent study conducted by Rotschild *et al* (2022) in Israel, revealing an OR 0.997 (95% CI 0.962 to 1.034) for a long-term exposure to CCBs (above 8 years) and breast cancer risk.^19^ A non-significant association was found in US women aged 55+ years for CCB use but a protective effect for ACEI use.^20^ However, a study by Gómez-Acebo *et al*
21 using Spanish data found CCB use for 5 or more years was associated with a 1.77 times increased risk (95% CI 0.99 to 3.17) of breast cancer. A 2021 systematic review of clinical trials showed no strong effect of any type of AHT medicine on breast cancer with a median follow-up of 4.2 years. However, a systematic review of cohort studies with longer follow-up (≥10 years) published in the same year found that the use of beta blockers, CCBs and diuretics was associated with increased breast cancer risk.^22^ The authors noted the heterogeneity of study design, study duration and capture of drug exposure status and also that most studies were from Europe or North America, limiting external validity.

Recommendations for CCB use are different across countries. CCBs are currently the second most commonly prescribed AHT medicine and are considered first-line treatment for hypertension in Australia.^23^ In contrast, CCBs are not recommended for first-line therapy in the Netherlands, where thiazide diuretics are more commonly initially prescribed for blood pressure control^24^ and this represents an opportunity to investigate the role of prescribing practices in cancer risk. Variations in prescribing patterns may drive the differences in the associations observed in studies of CCB use and risk of breast cancer across populations in addition to differences in underlying cancer risk due to varying environmental or biological/genetic factors (eg, body mass index (BMI), physical activity, smoking and alcohol history, hormonal medicine use or mammographic density). We expect this to be true for CCB prescribing in Australia compared with The Netherlands. The similarities and differences between the Dutch and Australian cohorts have been leveraged previously in studies of medicine safety.^25^ We therefore propose to use data from these two countries to (1) explore confounding and (2) effect modification by these specific factors in the relationship between CCB use and breast cancer risk.

Long-term evaluation of medicine safety is best monitored via longitudinal pharmacovigilance and observational studies, as they have both linked claims data and good confounder adjustment obtained through surveys of participants whereas randomised clinical trials with sufficient follow-up are largely not feasible due to time and cost factors. Thus, we aim to examine whether long-term CCB use is associated with the development of breast cancer among women enrolled in three longitudinal cohort studies in Australia and The Netherlands and to characterise the dose–response nature of any such association. A secondary aim is to assess whether any differences in the association between CCB use and the development of breast cancer exist between Australian and Dutch women and, if so, to explore confounding and effect modification for a range of socioeconomic and clinical factors.

## Methods and analysis

### Study design

This will be a retrospective, observational study conducted across three internationally renowned longitudinal cohorts incorporating both self-report and administrative data linked at the person level. For the primary aim, the study will use a distributed methodological approach, which has been shown to assure methodological quality and transparency and increase the likelihood that differences between results are due to true variation in effect size, rather than design or process‐related problems.^26^ Our analysis will (1) first use identical protocols across cohorts (harmonised analyses) and then (2) use variable/cohort-specific protocols to allow the influence of cohort-specific variables to be investigated (non-harmonised analyses).

### Data sources

We will use data from the Australian Longitudinal Study on Women’s Health (ALSWH),^27^ the New South Wales (NSW) Sax Institute’s 45 and Up Study (45 and Up Study)^28^ and the Rotterdam Study.^29^

The ALSWH^27^ is a national study that began in 1996 with a random sample of more than 40 000 women in 3 birth cohorts. The surveys were conducted every 3 years since 1996; however, the 1921–1926 cohort was surveyed 6 monthly from November 2011 for health and lifestyle changes. In our study, we will use two longitudinal cohorts, the 1946–1951 cohort (aged 45–50 years at recruitment) and the 1921–1926 cohort (aged 70–75 years at recruitment).Administrative data for the ALSWH are included for all Australian states and territories, linked using probabilistic linkage with clerical review by the data linkage units in each state. Linked data used for this study include hospital admissions, emergency department presentations, cancer registry and the national death index data. Hospitalisation and cancer registry data are recorded separately in each Australian state; hence, the start and end of these datasets vary according to the availability of the data in each state. Medicare Benefits Schedule (MBS) claims and Pharmaceutical Benefits Scheme (PBS) data were provided by Services Australia.The 45 and Up Study^28^ is a longitudinal cohort of 267 357 participants aged ≥45 years residing in NSW, Australia at recruitment randomly sampled from the Services Australia Medicare enrolment database. Participants from rural and remote areas and those 80+ years of age were oversampled. Participants were recruited from 2005 to 2009 (2005 being a pilot study) and followed up every 5 years for changes in health and lifestyle. The response fraction was approximately 19%. Only female participants (53.6% of the cohort) recruited in the main study between 2006 and 2009 will be included in the proposed study.Survey data for the 45 and Up Study were linked to the NSW Admitted Patient Data Collection and the Australian Capital Territory (ACT) Admitted Patient Collection, the NSW and ACT Emergency Department Data Collection, the NSW and ACT Cancer Registry, the NSW and ACT Registry of Births Deaths & Marriages death registrations, the Australian Coordinating Registry Cause of Death Unit Record File, NSW and ACT BreastScreen and the NSW Pap Test Registry by the Centre for Health Record Linkage using a probabilistic linkage procedure with clerical review. The current estimated rate of false-positive linkages is 0.5% (www.cherel.org.au). Linkage of 45 and Up Study cohort data to Medicare claims and PBS data provided by Services Australia was facilitated by the Sax Institute using a unique identifier and deterministic matching.The Rotterdam Study^29^ is a prospective cohort study of persons aged ≥45 years living in the city of Rotterdam, The Netherlands. The study started with a pilot phase in the second half of 1989, called ‘RS-I’. A second cohort was recruited in 2000 (RS-II) and a third cohort in 2006 (RS-III). By the end of 2008, the Rotterdam Study comprised 14 926 participants aged 45 years or over. At baseline, participants were interviewed and had a clinical examination that was repeated every 3–4 years. Follow-up of participants between clinical examinations is undertaken via automated coupling of the study database with medical records from general practitioners (GPs), who receive all relevant medical information from all caregivers of their patients. The data include hospital and specialist discharge summaries providing dates of diagnoses and major surgical interventions. Only female participants of the three longitudinal cohorts will be included in our study.The three Rotterdam longitudinal cohorts are linked at the individual level to records for dispensed medicines from all pharmacies in the study area (1991–2018), the Netherlands Comprehensive Cancer Organisation (1989–2016) and municipality (death) records (1989–2023).

A summary of the source of the major categories of data available for the study is provided in table 1.

**Table 1 T1:** Sources of data for the study

Data source	Sociodemographic characteristics	Lifestyle characteristics	Clinical characteristics	Reproductive health	Family history of cancer and genetic predisposition	Healthcare utilisation	Diagnosis of breast cancer	Medication use	Death
Self-report survey/clinical examinations	x	x	x	x	x		x	x	
PBS/pharmacy data			x					x	
Cancer Registry data			x				x		
MBS data			x			x			
GP records			x			x	x		
Hospital admission data			x			x	x		
Mortality register data									x

PBS, Pharmaceutical Benefits Scheme; MBS, Medicare Benefits Schedule; GP, general practitioner.

### Study population

The same study population will be used for the primary and secondary aims. Entry to our study will be on survey completion date for women who participated in the ALSWH survey waves between 2004 and 2008 or the 45 and Up Study baseline survey between 2006 and 2009 or the date of the Rotterdam Study interview and clinical examinations for women who completed these between 2004 and 2008. Inclusion criteria will be women who at entry to our study (1) were alive and consented to linkage of administrative data, (2) have evidence of hypertension from either self-reported hypertension (Australian longitudinal cohorts) or have a recorded diagnosis of hypertension in clinical examination data (Rotterdam cohorts).

Women will be excluded at entry if they had (1) history of primary invasive/in situ breast cancer or cancer that is metastatic to the breast; or (2) history of bilateral mastectomy; or (3) evidence of CCB use prior to entry. Further exclusion criteria will be applied in Australian longitudinal cohorts only as per standard practice when using PBS data: (1) women with any evidence of being Department of Veterans’ Affairs (DVA) concession card holders, because DVA-subsidised prescriptions are funded separately and not captured in the PBS data held; or (2) women who did not have evidence of concessional healthcare status for more than 1 year during period from 2003 to 2012. Those with concessional status, for example, those receiving the aged care pension or certain other government benefits, have lower copayments for PBS-listed medicines in comparison to ‘general beneficiaries’. This exclusion is necessary because some AHT medicines fall below the PBS copayment threshold for general beneficiaries, hence attracted no government reimbursement and were not captured in PBS data prior to an administrative change in 2012.^30^ In contrast, the lower copayment threshold for concessional patients means that AHT medicines can be captured throughout the study period.

Participants will be followed until the earliest date of one of the following: the outcome (a diagnosis of invasive breast cancer); a competing risk event (evidence of bilateral mastectomy without a diagnosis of breast cancer, death prior to any diagnosis of breast cancer) or end of the study follow-up (censoring event), whichever came first. Note that since the duration of the available data differs across the longitudinal cohorts, end of study follow-up will be established for each person based on the data available. Figure 1 presents a schematic diagram of timeline for entry, exposure and study exit (ie, recording of the outcome, censoring, competing event or end of follow-up) of our study population.

**Figure 1 F1:**
[figure not shown]
Schematic diagram showing entry, exposure and exit of the study populations across longitudinal cohorts. CCB, calcium channel blockers.

As administrative data are available prior to entry, this allows for a ‘lookback’ period to ascertain some aspects of health service use prior to study entry, for comorbidity ascertainment and to remove those with a history of CCB use or breast cancer diagnosis prior to time-zero for follow-up.

### Harmonisation of data

Harmonisation of data will be undertaken using the six-step process described by Rolland *et al*
31 and Fortier *et al*.^32^ After obtaining approvals from all data access and ethics committees, the Australian data will be housed in cohort-specific folders in the Sax Institute’s Secure Unified Research Environment (https://www.saxinstitute.org.au/solutions/sure/), whereas the Rotterdam data will be uploaded and analysed in the Accessible Network Digital Research Environment Alliance (www.andrea-cloud.eu). Related documents such as data processing scripts and comments on specific decisions taken throughout the process will be recorded. An associated data dictionary will also be developed. To ensure content equivalence, each variable will be checked on (1) the definition used in the questionnaire, format, categories, unit and time frame, (2) measurement method (eg, self-reported, clinical examination, etc) and (3) harmonisation rules. Variables relating to the main exposure, outcomes/competing risk, sociodemographic, lifestyle, clinical, reproductive characteristics and healthcare utilisation that are harmonisable, together with those available for the cohort-specific analyses, are presented in table 2. Where a variable has different categories across cohorts, we will collapse categories to generate the closest possible match.

**Table 2 T2:** Variables for harmonised and cohort-specific analyses

	ALSWH		45 and Up Study	Rotterdam study			Harmonisable status
	1946–1951 Cohort	1921–1926 Cohort		RS-I-4	RS-II-2	RS-III-1	
Sociodemographic characteristics							
Age	Y	Y	Y	Y	Y	Y	Y*
Marital status	Y	Y	Y	Y	Y	Y	Y*
Country of birth	Y	Y	Y	N	N	N	N
Socioeconomic disadvantage	Y	Y	Y	Y	Y	Y	Y*
Remoteness	Y	Y	Y	NA	NA	NA	Y*
Work status	N	N	Y	Y	Y	Y	N
Education status	Y	Y	Y	Y	Y	Y	Y*
Lifestyle characteristics							
Body mass index (height/weight)	Y	Y	Y	Y	Y	Y	Y*
Physical activity	Y	Y	Y	N	N	Y	N
Smoking status	Y	N	Y	Y	Y	Y	N
Alcohol drinks per week	Y	N	Y	Y	Y	Y	N
Shift work at night	Y	N	N	N	N	N	N
Clinical characteristics							
High BP	Y	Y	Y	Y	Y	Y	Y*
Systolic BP/diastolic BP	N	N	N	Y	Y	Y	N
Blood cholesterol level	N	N	N	Y	Y	Y	N
Diabetes	Y	Y	Y	Y	Y	Y	Y*
Heart disease	Y	Y	Y	Y	Y	Y	Y*
Stroke	Y	Y	Y	Y	Y	Y	Y*
Family history of heart disease	N	N	Y	Y	Y	Y	N
Family history of stroke	N	N	Y	Y	Y	Y	N
Mastectomy	Y	Y	Y	Y	Y	Y	Y*
Reproductive health							
Age at menarche	Y	N	N	Y	Y	Y	N
Age at menopause	Y	N	Y	Y	Y	Y	N
Age when had first child	Y	N	Y	Y	Y	Y	N
Number of children	Y	Y	Y	Y	Y	Y	Y*
History of hysterectomy/both ovaries removed	Y	Y	Y	Y	Y	Y	Y*
Breast feeding	N	N	Y	Y	Y	N	N
Healthcare utilisation							
Concession status	Y	Y	Y	NA	NA	NA	Y*
Mammogram	Y	N	Y	N	N	N	N
Hospital admissions	Y	Y	Y	N	N	N	N
Specialist/consulting physician attendances	Y	Y	Y	N	N	N	N
GPs attendances	Y	Y	Y	N	N	N	N
Diagnosis of cancer							
A diagnosis/history of invasive breast cancer	Y	Y	Y	Y	Y	Y	Y*
A diagnosis/history of non-invasive breast cancer (LCIS, DCIS)	Y	Y	Y	Y	Y	Y	Y*
Other cancer	Y	Y	Y	Y	Y	Y	Y*
Medicine use							
CCB	Y	Y	Y	Y	Y	Y	Y*
Non-CCB (ACEI, ARB, BB, diuretics, others)	Y	Y	Y	Y	Y	Y	Y*
Statins	Y	Y	Y	Y	Y	Y	Y*
Current use of combined hormonal contraception	Y	Y	Y	Y	Y	Y	Y*
Current use of combined menopausal hormone therapy	Y	Y	Y	Y	Y	Y	Y*
Comorbidity (Rx-Risk) score	Y	Y	Y	Y	Y	Y	Y*
Mortality							
Death	Y	Y	Y	Y	Y	Y	Y*

This table includes all potential confounders available from ALSWH (https://alswh.org.au/for-data-users/data-documentation/data-dictionary/), 45 and Up Study (https://www.saxinstitute.org.au/solutions/45-and-up-study/use-the-45-and-up-study/data-and-technical-information/), and Rotterdam Study (https://www.erasmusmc.nl/en/research/core-facilities/ergo-the-rotterdam-study).

*These variables will be used in the harmonised analysis.

†Comorbidity (Rx-Risk) score includes 46 clinical conditions based on prescribed medicine claims data.

ACEI, ACE inhibitors; ALSWH, Australian Longitudinal Study on Women’s Health; ARB, angiotensin receptor blockers; BB, beta blockers; BP, blood pressure; CCB, calcium channel blockers; CVD, cardiovascular disease; DCIS, ductal carcinoma in situ; FNA, fine-needle aspiration; LCIS, lobular carcinoma in situ; N, no data available; NA, not applicable; Y, Yes, data available.

### Exposure ascertainment

The exposure in this study, for both the primary and secondary aims, will be CCB dispensing including both combination and monotherapy products. Exploring the impact of confounding by indication for non-CCB AHT medicines is important because a modest increased risk of cancer in individuals with hypertension has been documented.^33^ To avoid this issue, previous studies have used a comparator group of patients exposed to other AHTs and/or with a hypertension diagnosis.^34^ Our study population is defined by the presence of hypertension since comparing only to a reference AHT medicine group risks biasing towards the null, if the comparator drug is associated with the outcome. Thus, to reduce bias to the null, women who are both AHT and CCB naïve will be included in the study as long as they meet the entry criteria of hypertension at baseline as described previously. To ensure that exposure to other AHT medicines is accounted for, the cumulative dose-duration exposure of other prescribed AHT medicines (combined) will be captured in the same way as that described for CCB exposure. Thus, in our study, the following four exposure states will be possible during follow-up: (1) women with no exposure to either CCBs or other AHTs; (2) women exposed to other AHTs but not exposed to CCBs; (3) women exposed to CCBs but not exposed to other AHTs and (4) women exposed (at any time) to both CCBs and AHTs. To compensate for immortal-time bias, and to be able to capture the dose–response nature of the association of CCB exposure with risk of breast cancer, a time-varying continuous ascertainment of cumulative exposure (dose duration) to CCB (and separately other AHTs) will be captured as follows.^35^

We will use the Anatomical Therapeutic Chemical (ATC) codes^36^ and information on dispensed medicines in the PBS data for Australian longitudinal cohorts and medicine record data for the Rotterdam longitudinal cohorts to identify AHT drugs dispensed for the study population from study entry to exit. We will categorise AHT drugs dispensed into five main AHT drug classes: (1) beta‐blocking agents (ATC code C07), (2) CCB (C08); (3) diuretics (C03), (4) agents acting on the renin–angiotensin system (ACEIs and ARBs) (C09), or (5) other AHTs not included in these classes regardless of treatment therapies (ie, monotherapy or combination therapy). Details of level 5 ATC codes of the dispensing medicines are presented in online supplemental appendix table 1.

10.1136/bmjopen-2023-080982.supp1Supplementary data

For all longitudinal cohorts, the total cumulative duration exposed and the total cumulative dose of each AHT drug class will be calculated from the medicine records available from entry to exit of the study. For all cohorts, the data include information on the date of dispensing, quantity dispensed and the strength of the medicine (derived from the PBS item code for Australian data). In the Rotterdam data, the daily prescribed dose and prescribed duration of use are also available.^29^ This information is not present in the Australian data necessitating estimation of the duration of the medicine. For the Australian data, the reverse waiting time distribution method with multiple random index dates will be used to determine the following: (1) the median duration of medicine possession, defined as the number of days that 50% of prevalent users of the same medicine refill their scripts and (2) the upper duration limit of medicine possession, defined as the number of days that 80% of prevalent users of the same medicine refill their scripts.^37 38^ The median duration will be used as the usual possession duration of the medicine in calculating the total duration (days) of medicine possession in contiguous periods of exposure. The contiguous period will be defined as a series of dispensings of the same AHT class with no break between dispensing that is greater than the upper duration limit of medicine possession of the last medicine in the series. The total cumulative duration (days) of exposure to each AHT class under investigation for each individual over the study period will be the sum of the number of days accrued over all contiguous periods of exposure. The total cumulative dose will be similarly captured across all contiguous periods of exposure by summing the total milligrams (mg) of medicine dispensed of all dispensations (strength/unit multiplied by total units dispensed).

Contiguous periods of exposure will account for any carryover of oversupply. The carryover will only be applied if the next dispensing is the same medicine (same ATC code at the fifth level) as suggested previously.^39^ The start of contiguous periods will be deemed the date of first-time dispensing observed within a series. End of a contiguous period will be the last dispensing date in the series plus the usual duration of medicine possession and any eligible carryover or the date of exit of the study where the duration of medicine possession continues past this date. Details of cumulative dose and duration are presented in figure 2.

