### Sensitivity analyses

We will conduct several sensitivity analyses. Since hyperplasia and atypical lesions are not precancerous, we will test the effect of adding ductal carcinoma in situ as a competing risk in sensitivity analyses rather than as an exclusion criterion. We will explore the impact of imposing various time lags, based on clinical consultation, between the start of follow-up on the outcome to account for latency and plausible timing between exposure and outcome development. The potential impact of reduced exposure resulting from imperfect adherence and prescribing at defined daily dose levels (a statistical measure of drug consumption, defined by the WHO) will be investigated in the dose-duration models and through sensitivity analyses.^36^ We will expand the study population to women with prior CCB use at entry (captured as a starting dose-duration value using available look-back data) to examine the impact of CCB use (overall) on the outcome. Finally, because concessional status for subsidised medicines in Australia can change with age or employment status, we will explore varying the definition of continuous PBS concessional status in Australian women to determine the impact this has on the association of CCB exposure with the outcome. The main analysis for the study will be evidence of 100% concessional status between 2003 and 2012 with a single year of no evidence allowed (ie, at least one dispensation per year, and patient recorded as being on concessional status on each dispensation, with 1 year allowed to vary). This will be varied allowing 2 years of no evidence (the more relaxed scenario) and requiring 100% concessional status across all years (as the most stringent requirement). Sensitivity analyses will be applied to the primary aim in the first instance, and those factors found to be influential will be additionally tested in the secondary aim. Due to the potential duplication of participants who were part of the ALSWH and also enrolled in the 45 and Up Study residing in NSW, we will systematically exclude ALSWH participants residint in NSW in a sensitivity analysis. This exclusion is essential for evaluating the potential impact of duplication on the study results.

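### Use of other antihypertensives before entry is not counted, excluded or adjusted for, so the CCB estimate keeps confounding by earlier treatment, of unknown direction

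*Protocol article*

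**What the plan says.** All references are to the protocol article.

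- **Window.** Under Exposure ascertainment, dispensing records serve "to identify AHT drugs dispensed for the study population from study entry to exit". Total duration and dose of each drug class "will be calculated from the medicine records available from entry to exit of the study". For the other antihypertensives, the "cumulative dose-duration exposure of other prescribed AHT medicines (combined) will be captured in the same way as that described for CCB exposure".
- **Eligibility.** Under Study population, women must at entry "have evidence of hypertension from either self-reported hypertension (Australian longitudinal cohorts) or have a recorded diagnosis of hypertension". The exclusion list contains "evidence of CCB use prior to entry" but no counterpart for any other antihypertensive class.
- **Look-back.** The text after Figure 1 gives pre-entry data to some measures of health service use, to comorbidity, and to removing women with earlier CCB use or breast cancer. Earlier use of other antihypertensives is not named.
- **Baseline adjustment.** The Covariates section lists no earlier antihypertensive use and no duration of hypertension or treatment. The Rx-Risk score has a 5-year look-back, but antihypertensives are removed from it because the exposure variable is said to hold them.
- **Sensitivity analysis.** Women with prior CCB use are to be admitted, with that use "captured as a starting dose-duration value using available look-back data". No such step is planned for other antihypertensives.
- **Limitation.** The strengths and limitations box and the Discussion concede that prior exposure cannot be fully known, but draw a consequence for CCB only.

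**The concern.** The plan gives its measure of other antihypertensives an explicit purpose: "To ensure that exposure to other AHT medicines is accounted for, the cumulative dose-duration exposure of other prescribed AHT medicines (combined) will be captured". A measure that starts at zero for every woman cannot do this in a population that already has hypertension at entry, where some women will have been treated for years.

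A CCB started after entry may be added to, or replace, earlier treatment, so treatment history may be linked to exposure. It may also be linked to the outcome: the Introduction cites a review of longer cohort studies in which "the use of beta blockers, CCBs and diuretics was associated with increased breast cancer risk". A variable linked to both is a baseline confounder, which the propensity score is there to balance. Treatment recorded after entry is not a full substitute, because it can itself change when a CCB is started.

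The research question lies close to the null. The Introduction reports one long-term estimate of 0.997 with a 95% interval of 0.962 to 1.034, so a residual bias of a few per cent would matter to the interpretation.

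**Working it through.** The plan gives no figure on this point to reproduce. The check has three steps.

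**1. What the written rule records.** Recorded other-antihypertensive years equal post-entry years; true years equal pre-entry plus post-entry years.

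| Years before entry | Years after entry | True | Recorded | Recorded the same as |
|---|---|---|---|---|
| 0 | 5 | 5 | 5 | (correct) |
| 10 | 5 | 15 | 5 | a new user with 5 years |
| 10 | 0 | 10 | 0 | a never user |

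The woman in the last row falls into the plan's first exposure state if she never takes a CCB, and into the third (CCB without other antihypertensives) if she does.

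**2. Whether another part of the plan repairs it.**

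- Exclusion at entry: CCB only.
- Baseline covariates: no earlier antihypertensive use.
- Rx-Risk: looks back 5 years, but these drugs are taken out. The reason given is valid after entry only, so pre-entry treatment drops out of both the score and the exposure.
- Table 2 marks non-CCB antihypertensives as harmonisable but states no pre-entry measurement.
- Starting value from look-back: CCB only, in a sensitivity analysis.

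None of these closes the gap in the harmonised analysis.

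**3. How large the confounding could be.** Treat pre-entry use as an unmeasured yes/no confounder within levels of recorded exposure. Let RR be its risk ratio for breast cancer, and p1 and p0 its prevalence in women with and without later CCB use. The bias factor on the CCB risk ratio is

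[p1(RR − 1) + 1] / [p0(RR − 1) + 1].

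The documents give none of these inputs; every value below is an assumption.

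| p1 v p0 | RR 1.0 | RR 1.1 | RR 1.2 | RR 1.5 |
|---|---|---|---|---|
| 50% v 50% | 1.00 | 1.00 | 1.00 | 1.00 |
| 60% v 40% | 1.00 | 1.06/1.04 = 1.02 | 1.12/1.08 = 1.04 | 1.30/1.20 = 1.08 |
| 80% v 40% | 1.00 | 1.08/1.04 = 1.04 | 1.16/1.08 = 1.07 | 1.40/1.20 = 1.17 |
| 40% v 80% | 1.00 | 1.04/1.08 = 0.96 | 1.08/1.16 = 0.93 | 1.20/1.40 = 0.86 |

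The last row describes CCB starters who were less often treated before entry, for example because the CCB was their first drug. The Introduction says CCB are first-line in Australia and not in the Netherlands, so the direction could even differ between cohorts.

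The formula applies to a risk ratio with a binary confounder. For the planned competing-risks model with continuous exposure it indicates order of magnitude only.

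**The case against.** **The evidence that other antihypertensives matter is mixed.** The Introduction also cites a review of clinical trials showing no strong effect of any class (median follow-up 4.2 years) and a study with a protective effect of ACE inhibitors. The Discussion cites genetic studies finding no association. Because the classes are combined, opposite effects could partly cancel. This stands: the bias may be nil, and no size can be claimed from the documents.

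**Continuing users are still classed as exposed.** This also stands. For them the error lies in the amount, not in the state. Only former users who do not restart are placed in the wrong state.

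**The plan partly concedes the point.** It admits incomplete prior exposure, and in the cohort-specific analyses it will explore earlier entry, which would count some use that now precedes entry. But the admission is applied to CCB only, and earlier entry is an exploratory step under the secondary aim.

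**The detail may sit in an unseen analysis plan.** A full covariate list could. However, the entry-to-exit window and the reason for removing these drugs from Rx-Risk are stated rules, and together they leave pre-entry treatment nowhere.

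**Look-back may recover little in Australia.** The plan secures capture by requiring concessional status over 2003 to 2012, because some antihypertensives bought by general beneficiaries were not recorded before 2012. Assured capture is then about 1 year for a 2004 entrant (2004 − 2003) and 3 years for a 2006 entrant (2006 − 2003), against 13 years in Rotterdam (2004 − 1991). With a 1-year window, the woman with 10 years before and 5 after is recorded as 6 of 15 years; with a 5-year window, as 10 of 15. This stands and limits what the fix can promise.

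**Conclusion.** The point holds as a gap in baseline adjustment. Pre-entry use of other antihypertensives is allowed, left out of the cumulative measure, absent from the baseline covariates, and removed from the comorbidity score for a reason that fails before entry. Long-standing users look like new users, and former users who do not restart look unexposed.

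With assumed risk ratios of 1.1 to 1.5 and the prevalence contrasts shown, the bias factor on the CCB estimate runs from about 0.86 to 1.17. It is exactly 1 if prior use is unrelated to breast cancer or to starting a CCB.

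A reader might infer that the CCB estimate will be biased upwards. The documents do not support that: they give neither the link between prior treatment and CCB start nor a settled effect of these drugs on breast cancer. Nor do they support the inference that a common look-back window would restore an unbiased estimate, since Australian history is too short for early entrants. The change should be made, but the gap does not invalidate the design.

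**What to change.** 1. Add pre-entry use of other antihypertensives (none, former, current, and observed length) from the available look-back to the baseline propensity model.
2. Use look-back to separate former users from women with no observed earlier treatment, and keep the term naive for the latter.
3. Start the cumulative dose and duration of other antihypertensives at a look-back value, as already planned for CCB, at least in a sensitivity analysis.
4. Correct the stated reason for removing antihypertensives from Rx-Risk, or point to the new pre-entry covariate.
5. Extend the limitation on prior exposure to other antihypertensives.

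The cost is plan wording and some programming. Pre-entry dispensing records are already needed to exclude prior CCB users and to compute Rx-Risk. The downside is that a look-back common to all cohorts must be short, because concessional status is assessed from 2003 and entry starts in 2004. The harmonised analysis would then recognise current users but miss much former use and most of the length of treatment. The non-harmonised analyses can use longer cohort-specific look-back, such as the Rotterdam pharmacy records from 1991, and show how much the CCB estimate moves.
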